### Participants

We plan to recruit 100 children (boys and girls) and their mothers. The inclusion and exclusion criteria for the children are listed below:

Inclusion criteria:Age 8–12 yearsCapable of comprehending and reading the Dutch language

Exclusion criteria:Known OT allergyCurrently using medicationKidney or cardiac condition

### Procedure

We will recruit children via the distribution of flyers at local schools, youth clubs and events, the local university and hospital. After stating interest to participate, mothers receive information about the study in general and about OT specifically via email. Subsequently, the researchers contact mothers by phone and explain the procedure verbally, check inclusion and exclusion criteria and address any questions or concerns. When eligible, we invite mother and child to participate and schedule a testing appointment. We ask mothers to make sure that the child abstains from caffeine for at least 2 h before study onset.

Upon arrival at the laboratory, mother and child complete a written informed consent (see Additional file 3 for the Informed Consent Form) and assent respectively. The child’s procedure consists of (1) a pre-intervention puzzle task, (2) a pre-intervention trust questionnaire, (3) a pre-intervention recognition task, (4) nasal spray administration, (5) a 35-min break, (6) training, (7) a post-intervention recognition task, (8) a post-intervention trust questionnaire, (9) a post-intervention puzzle task and (10) a side-effects questionnaire. The mother is present for the pre-intervention puzzle task, after which she retreats to a different room to fill out a questionnaire booklet. She only returns when it is time to start with the post-intervention puzzle task. The entire procedure lasts approximately 120 to 150 min. At the end of the procedure, participants receive two cinema tickets in gratitude for their participation. See Fig. 1 for a flowchart of the child’s and mother’s procedure.

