The trial takes place at the Parenting and Special Education Research Unit, KU Leuven, Belgium. The Medical Ethics Committee UZ KU Leuven/Research (S57012) approved the study design in accordance with the Declaration of Helsinki. We submit any protocol amendments and progress reports to the Ethics Committee as required, as well as an end-of-study declaration. We registered the trial in the database of ClinicalTrials.gov (NCT02737254). The Belgian Federal Agency for Medicines and Health Products also approved the trial. See Additional file 1 and Table 1 for a checklist and an overview of study procedures in line with Standard Protocol Items: Recommendations for Interventional Trials (SPIRIT) [50] and Additional file 2 for a description of all items from the World Health Organization Trial Registration Data Set.

**Table 1 Tab1:** Schedule of enrollment, interventions and assessments in line with Standard Protocol Items: Recommendations for Interventional Trials (SPIRIT)

	Study period				
	Enrollment	Allocation	Post-allocation		
Timepoint	Before intervention (baseline)	0	During intervention	Immediately after intervention	24 h after intervention
Enrollment:					
Eligibility screen	X				
Informed consent	X				
Allocation		X			
Interventions:					
CBM training + OT			X		
CBM training + PL			X		
Neutral training + OT			X		
Neutral training + PL			X		
Assessments:					
Interpretation speed of secure and insecure scenario resolutions			X		
Secure interpretation bias	X			X	
Insecure interpretation bias	X			X	
Trust (PIML)	X			X	
Puzzle task	X			X	
Mood	X		X	X	
OT side-effects				X	X
Mother-reported questionnaires:					
Demographic questionnaire			X		
Child temperament (EATQ-R)			X		
Child behavioral and emotional problems (CBCL)			X		
Parenting questionnaires (VSOG, subscales LAPPS, POPS, PCS)			X		
Pubertal development (PDS)			X		
Symptoms of sino-nasal problems (Snot-20)			X		

*CBCL* Child Behavior Checklist, *EATQ-R* Early Adolescent Temperament Questionnaire-Revised, *LAPPS* Louvain Adolescent Perceived Parenting Scale, *OT* oxytocin, *PCS* Psychological Control Scale, *PDS* Pubertal Developmental Scale, *PIML* People In My Life, *PL* placebo, *POPS* Perceptions of Parents Scale, 20-*Snot-20* 20-item Sino-Nasal Outcome Test, *VSOG* Verkorte Schaal Ouderlijk Gedrag

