##### Change in observed behavior during a distressing task

We assess changes in behavior of children towards mother and in mother-child interactional behavior by means of videotaped observation of mother-child interaction during a distressing puzzle task. Researchers have used this puzzle task, taken from Rush Hour Traffic Jam Puzzle®, before to observe attachment behavior in a distressing situation in middle childhood [58, 59]. In this task, a red car’s path out of a traffic jam is blocked by other cars and trucks. The child has to move the other cars to free the path for the red car. After the experimenter explains the rules, children first solve a simple practice puzzle. Subsequently the child receives an unsolvable puzzle with the instruction that their mother is allowed to help. The experimenter tells children that the puzzle is not very difficult, that most children their age can solve the puzzle in less than 5 min, and that, therefore, they are also given 5 min to solve the puzzle. A laptop screen shows a stopwatch so that the child can see how much time is left. The combination of trying to solve an unsolvable puzzle under time pressure and social comparison with peers effectively induced stress in previous research [59]. After starting the stopwatch the experimenter leaves the room. Three minutes later the experimenter returns and aborts the attempt to solve the puzzle with the excuse that, on account of the timing of the procedure, they have to proceed with the rest of the tasks. The experimenter then says that the mother-child dyad will be given another chance to solve the puzzle when there is time left at the end of the procedure. The attempt to solve the puzzle is terminated after 3 min instead of 5 min so children do not specifically fail on the first attempt, but are merely given too little time to solve it. This with the aim to increase comparability between the pre-intervention and post-intervention puzzle tasks.

We administer the same puzzle task post-intervention. Participants receive the same instructions as pre-intervention, after which the experimenter starts the stopwatch and leaves the room. Three minutes later the experimenter enters again and stops the attempt to solve the puzzle by asking the mother-child dyad whether they already succeeded in solving the puzzle. As a manipulation check the experimenter asks – first the child, then the mother – if they know how it is possible that they were not able to solve the puzzle.

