### Other measures

#### Oxytocin side-effects

We explore any side-effects of the OT intervention with parent and child questionnaires. All children are asked about the most common reported side-effects which include dizziness, drowsiness, dry mouth, irritated or runny nose, stomach- or headache, anxiety, feeling uplifted and feeling relaxed [53], and any other noted changes immediately after the procedure (face-to-face). After 24 h, mothers answer the same questions via phone. Experimenters register the onset, duration and severity of any reported side-effects.

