A limitation regarding the current study design is that effects of the interventions are assessed immediately after intervention. As a result, prolonged long-term effects of the interventions remain unknown. Similarly, since the current study consists of a single session, we cannot assess the impact of multiple sessions of the intervention(s). Without doubt, longer-term effects of OT administration and CBM are important to assess when considering them as clinical interventions to improve or rebuild trust. However, since previous research using the same CBM procedure yielded immediate effects on trust c, the current study was set up to test (1) whether OT can enhance these CBM effects and (2) whether OT as individual intervention has an immediate effect on trust. As the present study is the first to combine these two interventions, it is an important first step to assess the short-term effects and feasibility of a single intervention session. Nonetheless, if the (combined) interventions were to prove effective in the current study, future research will be crucial to explore the long-term effects of the interventions as well as the effect of multiple intervention sessions. Additionally, the effects of the interventions are tested in a normal population sample and, therefore, the effectiveness of the interventions in clinical groups cannot be ascertained from the current study. If the current study were to provide favorable results following the CBM and OT interventions, another important next step is to assess effects of the interventions in clinical samples.

In all, the current paper describes the protocol for a RCT investigating the individual and combined effects of CBM training and OT on trust in mother. Additionally, the current RCT tests the safety of OT administration in 8–12-year-old children. As OT studies in pediatric populations have yielded mixed results, with the current comprehensive protocol description we aim to expedite the clarity and reproducibility of OT research findings. If effective, CBM training and OT could be easily applicable and nonintrusive additions to interventions that target trust in the context of the parent-child relationship.

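### Side-effects are a stated aim, but the symptom checklist has no pre-spray reading and the child answers it only once, straight after a stress-inducing puzzle, which inflates raw rates and lowers sensitivity

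*Protocol article*

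**What the plan says.** The Procedure section lists ten steps for the child. The first puzzle is step 1, the spray is step 4, and the session ends with "9) a post-intervention puzzle task and (10) a side-effects questionnaire". The whole session takes about 120 to 150 minutes.

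In Table 1 (Study design), the row "OT side-effects" is marked only immediately after and 24 hours after the intervention. Interpretation bias, trust, the puzzle task and mood all have a baseline mark.

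The puzzle is unsolvable by design. The section on observed behavior says: "The combination of trying to solve an unsolvable puzzle under time pressure and social comparison with peers effectively induced stress in previous research".

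The section Oxytocin side-effects says: "All children are asked about the most common reported side-effects which include dizziness, drowsiness, dry mouth, irritated or runny nose, stomach- or headache, anxiety", and the list goes on to include feeling uplifted and relaxed. Onset, duration and severity are recorded, and mothers answer the same questions by phone at 24 hours.

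On the aim, the Discussion calls knowledge of side-effects an important additional aim and closes by saying that "the current RCT tests the safety of OT administration in 8–12-year-old children".

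**The concern.** Several items on the list (anxiety, headache or stomach-ache, drowsiness, feeling relaxed or uplifted) can plausibly be produced or suppressed by a stressful task or a long session. Others may be present when the child arrives. With no reading before the spray, a symptom reported at step 10 cannot be classed as new in an individual child.

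The other measures do not supply that baseline:

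- The mood scales cover only happy and sad.
- The Snot-20 is a mother's report of nasal symptoms over the past two weeks.
- The mother is in another room from the end of the first puzzle until the second, so her 24-hour answers do not rest on her own observation of that interval.
- Recorded onset helps, but for the same interval it rests on the child's recall.

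At stake is how the safety results are read. Oxytocin-arm percentages quoted alone would overstate what the drug does. A finding of no difference from placebo could be taken as more reassuring than the comparison allows. A baseline that was never taken cannot be recovered at the analysis stage.

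**Working it through.** **The plan's own figure.** The article gives no precision or power for side-effects. Its sample size is for the efficacy outcomes (Sample size section): f = 0.30, alpha .05, numerator df 1, four groups. With noncentrality f²N and N − 4 denominator df:

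- N = 90: noncentrality 0.09 × 90 = 8.1, critical F 3.95, power 0.803. This is the smallest N that reaches 0.80.
- N = 100: noncentrality 0.09 × 100 = 9.0, critical F 3.94, power 0.844.

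Both stated results (90 participants; 0.84 at 100) reproduce. With 25 children per cell, the spray comparison is 2 × 25 = 50 oxytocin v 50 placebo.

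**Does the timing bias the comparison?** No. If the procedure produces a symptom at the same rate in both spray arms, its expected contribution to the difference is zero. With Fisher's exact test at 50 v 50, the false-positive rate stays between 0.000 and 0.032 for assumed backgrounds from 1% to 40%.

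**What does background cost in precision?** If both arms have symptom rate p, the 95% half-width for the risk difference is 1.96 × √(2p(1 − p)/50):

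- p = 0.05: 1.96 × √0.0019 = 8.5 points
- p = 0.10: 1.96 × √0.0036 = 11.8 points
- p = 0.30: 1.96 × √0.0084 = 18.0 points

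**What does it cost in power?** Suppose oxytocin causes a symptom in 20% of children who would otherwise be free of it (an assumption). At background b, the oxytocin-arm rate is b + 0.20(1 − b).

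| Assumed background | Expected difference (points) | Power, normal approximation | Power, Fisher | Difference detectable with 80% power (points) |
|---|---|---|---|---|
| 1% | 19.8 | 0.90 | 0.89 | 16 |
| 10% | 18 | 0.63 | 0.55 | 23 |
| 20% | 16 | 0.43 | 0.35 | 26.5 |
| 40% | 12 | 0.22 | 0.18 | 28 |

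**What can 50 exposed children exclude?** With zero events, the upper limit is 1 − 0.05^(1/50) = 5.8% (one-sided 95%) or 1 − 0.025^(1/50) = 7.1% (two-sided). This bound depends on the sample size and not on when the checklist is given. It bears only on the wording of the safety claim.

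**The case against.** The best defense is the design itself. Half the children receive saline, all are asked the same questions ("All children are asked about the most common reported side-effects"), and the experimenters are blind to the spray. A reader might infer that the safety aim will be answered with symptoms the procedure creates. The documents do not support that: both spray arms go through the same puzzle and questionnaire, so those symptoms cancel in expectation. This part of the defense stands in full.

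Other points also stand, in part or in full:

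- The article gives no symptom rates, so the size of any rise caused by the puzzle is unknown. The attempt lasts three minutes, and nothing suggests that it causes a dry mouth or a runny nose.
- A reader might suppose that the child must recall two hours or more. The 120 to 150 minutes are the whole session, and the spray is step 4. The interval from spray to checklist is shorter than the total and is not stated.
- The 24-hour call and the recorded onset give some separation from the puzzle, though neither replaces a baseline.
- The questionnaire is not shown, so its items may already be phrased as changes. Even then, the change would rest on recall.
- Asking last is a defensible choice. A checklist between the trust questionnaire (step 8) and the second puzzle (step 9) could cue or unblind children just before a behavioral outcome.
- Elsewhere the article states the safety aim modestly, as exploring side-effects and adding information.

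None of this supplies a pre-spray reading.

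**Conclusion.** The point holds as a modest design weakness that is cheap to improve. It is neither a bias nor an internal contradiction. The symptom checklist has no pre-spray reading, and the child's only reading follows a deliberate stressor. Raw oxytocin-arm rates therefore cannot be read as drug effects, and background symptoms reduce the sensitivity of a small comparison.

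If the background rose from 5% to 30%, the half-width would roughly double (18.0/8.5 = 2.1). Both rates are assumptions, so this shows the scale of the problem and is not an estimate for this trial. The anxiety and relaxation items also describe the child's state after stress rather than tolerability at rest, and the placebo arm does not change that.

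That the Data analysis section describes no side-effect comparison is not counted against the plan, because a fuller document may contain one.

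**What to change.** For children still to be recruited (Trial status says that recruitment is open):

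1. Give the same short checklist immediately before the spray, after the pre-intervention recognition task (step 3).
2. Keep the end-of-session reading at step 10 and the 24-hour call. Do not add a checklist between steps 8 and 9.
3. Count as a side-effect any symptom that is new or worse since the pre-spray reading.
4. Report oxytocin-placebo differences with confidence intervals rather than raw oxytocin-arm rates.
5. In the last paragraph of the Discussion, qualify the claim to test safety by stating that zero events in 50 exposed children would exclude only reactions more common than about 6-7%.

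The change removes pre-existing symptoms only. For illustration, if half of a 10% background were already present before the spray and did not worsen, the counted rate would be 5% and the half-width would fall from 11.8 to 8.5 points. Symptoms caused by the second puzzle or the session length would still count as new, and the placebo comparison must deal with those.

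The cost is a few minutes of existing experimenter time and a minor amendment. There are three downsides. Naming symptoms early may cue children slightly in both arms. The first puzzle (step 1) also precedes the new reading, so an anxiety baseline may carry some of that stress. Children already enrolled lack the reading, so the new-or-worse analysis covers later children only, and its oxytocin and placebo groups will be smaller than 50 each.

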**Fig. 1 Fig1:**
[figure not shown]
Participant flowchart

### Interventions

#### OT intervention

The pharmacy of the University Hospital of Heidelberg, Germany prepares the study medication. Half of the participants receives OT (Syntocinon®, 40 international units (IU)/ml), the other half receives PL (0.9% sodium chloride solution). The bottles containing OT and PL are identical: 10-ml brown glass bottles, hydrolytic class type III, with DIN ND 18 screw thread. The nasal pump has a volume of 0.05 ml per puff. We weigh children on a digital personal scale and base the amount of nasal spray administered on the child’s weight. The conventional dose in adult studies is 24 IU OT, although a study comparing different doses in adults has shown that salivary OT levels were equally elevated after intranasal administration of 24 IU OT and of 16 IU OT [51]. Studies involving OT nasal spray in children (under 12 years) used doses varying between 8 IU and 24 IU. These studies based the amount of nasal spray administered on age as a proxy for weight [24], on weight [36], or gave all children the same (stepwise raised) amount of OT [39]. These studies either found that the results did not depend on OT dosage [36, 39] or did not report on dosage effects [24]. As it is most common to base drug doses in pediatric populations on weight [52], we used the same weight-based dosing strategy as in the study by Dadds et al. [36]: children weighing less than 40 kg receive 0.3 ml nasal spray (i.e., 12 IU OT for the OT condition); children weighing more than 40 kg receive 0.6 ml (i.e., 24 IU OT for the OT condition). Single administration of OT in dosage amounts up to 40 IU has not resulted in side-effects or adverse outcomes [53].

We based the nasal spray administration procedure on recommendations by Guastella et al. [54]. Before use, the experimenter primes the spray by pumping approximately seven to eight times until a fine mist is visibly released. After priming, the experimenter weighs the bottle on an apothecary scale (Kern EMB 200-2). Experimenters ask the children to keep their head upright or slightly tilted backwards during administration. Experimenters explain to the children that we will alternate administration between nostrils and that they have to keep the other nostril closed with one finger and inhale lightly two or three times upon nasal spray delivery. Child and experimenter practice this administration procedure together before actual administration. Either the experimenter, or the child itself under experimenter supervision, administers the spray. Experimenters make sure that the top of the nasal spray is inserted into the nose about 1 cm and that the bottle is held at a slight angle such that the pipe is well immersed in the fluid at all times. After 6 (for children under 40 kg) or 12 (for children over 40 kg) pumps, the experimenter weighs the spray again on the scale. If necessary, we administer extra pumps until at least 0.26 ml or 0.56 ml has been released from the bottle. Experimenters register the amount of nasal spray administered.

Subsequently, children wait for 35 min, during which they can choose to draw, read a comic or watch a video. During the break, experimenters make sure that children remain calm (e.g., do not watch exciting videos), do not eat or drink except for water, and are not in contact with their mother.

#### CBM intervention

After the break, children start a computerized training that either aims to positively modify their interpretation of maternal support-related behavior and subsequent trust in maternal support (CBM training condition) or aims to have no effect (neutral training condition). The same CBM training was effective in modifying attachment interpretation bias in the study by De Winter et al. [23]. During training (both conditions) children read, at their own pace, 42 short scenarios on a laptop. The scenarios describe situations in which middle childhood children might need maternal support [55]. All scenarios consist of three lines of text and in the last line a word is missing, rendering the outcome of the scenario ambiguous. On the next screen, the missing word is presented as a word fragment (i.e., one letter in the word is missing). The child’s task is to figure out what the word should be and hence which letter is missing. Children press the space button as soon as they know the missing letter. Subsequently, they press the missing letter on the keyboard. To make sure that children actively read the scenarios, they have to answer a yes/no comprehension question after each scenario, after which they receive feedback on their answer. The training consists of six blocks of seven scenarios each and children can take a short break in between blocks.

Every block consists of two probe scenarios that are the same for the two conditions (see “Outcome measures” below) and five scenarios that are different for the two conditions. In the CBM training condition each block contains five training scenarios that are aimed at increasing secure interpretation bias. As a result of the missing word in the last sentence it is unclear whether mother does or does not provide support. In these training scenarios the resolving word fragment is always secure, which trains the child to interpret ambiguous maternal behavior in a secure way. In the neutral training condition, each block contains five neutral scenarios. The first two sentences in these scenarios are similar to the training scenarios in the CBM condition. The last sentence, however, is unrelated to maternal support. Therefore, resolving the word fragment does not influence the child’s interpretation of mother’s behavior. For learning effects to occur, it is important to provide enough repetition for participants to be able to learn to interpret the ambiguous scenarios in a positive way, while at the same time not to overload participants in order to keep them attentive and motivated. The current distribution of 42 scenario’s over six blocks was both feasible and effective in modifying attachment interpretation bias and trust in the study by De Winter et al. [23].

